## Abstract

**Background:**

Globally, most strokes occur in low- and middle-income countries, such as India, with many affected people having no or limited access to rehabilitation services. Western models of stroke rehabilitation are often unaffordable in many populations but evidence from systematic reviews of stroke unit care and early supported discharge rehabilitation trials suggest that some components might form the basis of affordable interventions in low-resource settings. We describe the background, history and design of the ATTEND trial, a complex intervention centred on family-led stroke rehabilitation in India.

**Methods/design:**

The ATTEND trial aims to test the hypothesis that a family-led caregiver-delivered home-based rehabilitation intervention, designed for the Indian context, will reduce the composite poor outcome of death or dependency at 6 months after stroke, in a multicentre, individually randomized controlled trial with blinded outcome assessment, involving 1200 patients across 14 hospital sites in India.

**Discussion:**

The ATTEND trial is testing the effectiveness of a low-cost rehabilitation intervention that could be widely generalizable to other low- and middle-income countries.

**Trial registration:**

Clinical Trials Registry-India CTRI/2013/04/003557. Australian New Zealand Clinical Trials Registry ACTRN12613000078752. Universal Trial Number U1111-1138-6707.

**Electronic supplementary material:**

The online version of this article (doi:10.1186/s13063-015-1129-8) contains supplementary material, which is available to authorized users.

## Background

Stroke causes 6 million deaths each year among 17 million affected people, with the greatest burden experienced in populations of low- and middle-income countries [1]. In these countries, the burden of stroke is increasing, owing to lifestyle changes and rapid ageing of populations. Furthermore, stroke tends to affect people at relatively younger ages where there is poor control of established risk factors, in particular high blood pressure [2], with significant social and financial consequences for families, owing to limited financial protection from the costs of care and minimal social safety nets [3]. Stroke usually affects at least two people in a family, the patient and at least one family caregiver, with epidemic proportions of premature loss of productive lives in developing countries, such as India [4–6].

Like many developing countries, India is experiencing an epidemiologic transition, in which the burdens of infectious disease, maternal and child health problems are decreasing, while the burden of non-communicable chronic diseases, such as stroke and injury, is increasing [7]. In India, based upon an annual incidence of stroke of 135 to 145 per 100,000, and early case fatality of between 27 % and 41 % [7–10], it has been estimated that 1.5 million people experience stroke each year, and a further 500,000 people live with stroke-related disability. The long-term consequences of stroke on families in India, particularly in rural areas, are likely to be significant.

The most important treatment for patients with stroke is well-organized specialist care [11], which allows rapid and well-coordinated assessment and diagnosis [12, 13], early recognition and management of complications, early rehabilitation, education, and appropriate long-term support and secondary preventative therapy. Stroke unit care has greater public health impact than treatment with thrombolysis (alteplase) alone, even with the most optimal thrombolysis rates [11], because thrombolysis rates are rarely greater than 20 % (with a 5–10 % absolute benefit), yet stroke unit care is applicable to all (with a 5 % absolute benefit). Organized stroke care should be a public health priority in low- and middle-income countries, to ameliorate the increasing burden of stroke.

Although appropriate stroke unit care and rehabilitation may meet important clinical, physical and psychosocial needs during the early post-stroke phase, the needs of patients and families in the long term cannot solely be addressed in hospital [14, 15]. Advocates for early supported discharge and home-based stroke rehabilitation, which is based upon a coordinated stroke unit model of care, argue that it offers several advantages: satisfying patient choice; reducing risks (and costs) associated with inpatient care through reductions in length of hospital stay; a better rehabilitation setting, as the home setting is more focused towards realistic goals, social inclusion and a supportive environment; and leading to savings in direct and indirect costs [16, 17]. Early supported discharge provides a continuous process of rehabilitation that spans the in-hospital period and the weeks of resettlement and readjustment at home. A meta-analysis of 11 trials (mainly conducted in developed countries, where fully funded community rehabilitation teams are available) shows that early supported discharge services significantly reduced the odds of death or dependency by 21 % (odds ratio 0.79; 95 % confidence interval 0.64–0.97), without major adverse effects, either on patients or caregivers [17].

Although acute stroke units are increasing as resources improve in India, they meet the needs of only a tiny fraction of the country’s vast population, and the majority of Indians do not have access to rehabilitation services, either in hospital or following discharge. The development of effective low-cost community rehabilitation services for emerging major chronic diseases, such as stroke in India, has the potential for significant public health impact. Such interventions, if shown to be effective and affordable, could be widely scaled up or generalizable. Indeed, the research question of how to create sustainable and multiprofessional rehabilitation systems in low- and middle-income countries, including the provision of services to the rural population, was considered the second most important research priority (after equality of healthcare access) for disabled people in a recent *Lancet* expert panel [18]. Currently, most Indian stroke units are situated in the private sector [19, 20]. Clear evidence that low-cost interventions are cost-effective in India would facilitate their expansion within the public hospital system, where rehabilitation has some important features that differ from those in high-income countries: therapy is driven largely by physiotherapists, with limited input from other health professionals, such as occupational therapists; it is often poorly coordinated; and most people receive care within a large family unit (‘a joint family’, often called an extended family) after discharge [21].

A modified version of the Western model of early supported discharge, together with a development of the Indian-suggested solution based on rehabilitation delivered by a trained family caregiver, appears to be the most promising hybrid model of stroke care that could be widely implemented, if shown to be successful. Similar models have been shown to be cost-effective in the UK [22, 23]. To develop appropriate health policy, though, effectiveness and cost-effectiveness of any new model of care including rehabilitation needs rigorous evaluation in the relevant setting.

## Methods

The ATTEND study is a multicentre, prospective, individually randomized, blinded outcome assessed, controlled trial (prospective, randomized, open, blinded, endpoint design) of early supported discharge with a trained family-led caregiver.

The intervention is a stroke rehabilitation package of care that starts in hospital and continues at home, compared with usual care, in at least 1200 patients with mild to moderate disability recruited from 14 hospital sites across India.

The inclusion criteria are:Adults (≥18 years);Recent (<1 month) acute ischaemic, haemorrhagic or undifferentiated stroke;Residual disability (requiring help from another person for everyday activities);Expected to survive to discharge from hospital, with a reasonable expectation of 6 month survival (i.e. not palliative, no evidence of widespread cancer etc.);Able (or by proxy) to provide informed consent.

Exclusion criteria are:Unable to identify a suitable family-nominated caregiver for training and subsequent delivery of care;Unwilling or unable to adhere to follow-up.

### Randomization

Eligible patients are identified by the trial stroke coordinator (usually a physiotherapist) and medical coordinator. A patient information sheet (Additional file 1) is shared with the patient and nominated caregiver, and outlines the study objectives and risks and benefits to the patient or caregiver. Informed consent from each participant and his or her caregiver is obtained based on the International Conference on Harmonisation Good Clinical Practices guidelines (ICH/GCP) and ethical guidelines for biomedical research on human participants published by the Indian Council of Medical Research, New Delhi (Fig. 1). If the caregiver changes by the time of the 3- or 6-month follow-up periods, the new caregiver will be asked to provide consent for the caregiver aspects of follow-up after reading the patient information sheet. Stroke patients often do not have the capacity to consent, owing to the acute effects of stroke. Capacity for informed consent is assessed by the medically qualified principal investigator at each site. The ethics committee have approved ATTEND to obtain consent from a legally acceptable representative in such cases. Once consented, patients are randomized by the trial stroke coordinator to the intervention or control arm in a 1:1 ratio within 7 days of hospital admission, using a secure, central, password-protected, web-based system, stratified by centre and stroke severity.

**Fig. 1 Fig1:**
[figure not shown]
Study flow chart. ADL, activities of daily living; EQ-5D-3L, EuroQol 5-Dimensional, 3 Levels; NIHSS, National Institutes of Health Stroke Scale; WHOQOL-BREF, World Health Organization Quality of Life (Brief)

#### Intervention arm

Patients allocated to the intervention arm have their family-nominated caregiver trained by a specially trained trial stroke coordinator health professional (e.g., nurse, therapist) using a trial-specific structured assessment (cognition, language, function and mobility) and recommended rehabilitation package. The rehabilitation package includes a structured checklist and culturally appropriate manual (adapted to local Indian contemporaneous stroke practice) covering key activities relevant to daily living (e.g., positioning, transfers, mobilization, feeding, dressing, activity and motor practice, and monitoring of mood). Detailed instructions for selected training exercises are used from http://www.physiotherapyexercises.com. Training begins in hospital immediately after randomization for those allocated to the intervention, with a goal of approximately 60 min training per day for about 3 days, with the intention of accelerating the patient’s hospital discharge, when it is safe to do so, in addition to usual hospital care. The trial stroke coordinator visits the patient and caregiver’s home, if they are allocated to the intervention arm, on up to six occasions over the next 2 months, to provide guidance and to monitor progress after discharge, and is available by telephone for further support and guidance as the patient progresses.

A detailed written intervention guide, adapted from previous work [24], instructs all trial stroke coordinators in delivering the structured intervention in a standardized manner; this is reinforced at training sessions during the annual collaborators’ meetings.

The intervention components are:Information on stroke recovery trajectory, risk, identification and management of low mood, importance of repeated practice of specific activities.Positioning, transfers and mobility.Discharge planning.Joint goal setting with patient, nominated family caregiver and therapist (reviewed with coordinator as patient progresses and new goals set).Task-orientated training (particularly walking, upper limb and self-care tasks) with personalized copy of culturally appropriate manual.

The detailed intervention guide and manual are kept confidential and will only be published after the last patient follow-up has been completed, to avoid contamination of the control patients during the conduct of the trial.

#### Control arm

These patients will receive usual hospital care in terms of access to rehabilitation, timeliness of discharge and follow-up, without any explicit provision of accelerated discharge or caregiver training.

### Outcome measurement

The primary outcome measure is the effect of treatment allocation on death or dependency (a score of 0–2 on the modified Rankin scale [25]) at 6 months after randomization [26]. Patients will be seen after 3 and 6 months by an independent blinded assessor who will collect the primary and secondary outcome data.

Secondary outcome measures are:Effect of treatment on shift in disability, as measured by the modified Rankin scale, and analyzed with shift (ordinal) analysis;Answers to the simple validated recovery (Have you made a complete recovery from your stroke?) and dependency (Do you need help from another person for everyday activities?) questions [27];Hospital length of stay;Place of residence;Scores on the Barthel Index [26];Score on the Caregiver Burden Scale [28];Health-related quality of life (World Health Organization Quality of Life Assessment and EuroQol 5-Dimensional scores) [29, 30];Patient and caregiver mood (Hospital Anxiety and Depression Scale) [31];Extended activities of daily living (Nottingham Extended Activities of Daily Living Scale) [32];Health care resource use (visits to health professionals, hospitalization, and medication use) and direct costs for the patient (e.g. payment to the caregiver to act as carer for this patient, total direct costs of healthcare paid by the family since time of stroke);Indirect costs (e.g. family member giving up paid employment to act as caregiver) of the family;Direct medical costs (e.g. total expenditure during hospital admission, including first place where patient was taken, general or private admission, length of hospital stay, admission charges, investigation charges and drug treatment);Non-medical direct costs (e.g. travelling costs).

Clinic or telephone follow-up will be offered if home visits are not possible.

Data are collected on paper forms with an English translation on one side and the appropriate local Indian language on the other side. Each patient is identified by a unique identifier with only local sites holding the master log of names. The trial database is held and maintained by The George Institute for Global Health, with access for analysis determined by the steering committee. Future access to participant level data and statistical code will depend on additional funding to safeguard and prepare the data and is contingent upon compliance with data management guidelines in India and Australia.

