### Sample size and statistical consideration

In the meta-analysis of early supported discharge trials, the proportion of people dead or dependent at the end of follow-up was 50 % and the likely beneficial effect of early supported discharge treatment was an odds reduction of 21 % (95 % confidence interval 3–26 %). Therefore, the proposed minimum sample size of 1200 (600 per group) provides at least 90 % power (two-tailed α, 0.05) to detect plausible modest 10.5 % reductions in death or dependency in the intervention group with inflation by 20 % to account for patients dropping out of the trial. Ideally, a higher recruitment will allow a greater precision for treatment estimates, and could permit more detailed subgroup analysis; thus, when 1200 patients have been recruited, and if funding and time permits, the data and safety monitoring committee will advise on whether it is safe to continue recruitment. Experience during 2014 and early 2015 has allowed prediction that the trial will complete recruitment in early 2016, based on current strategies.

The intention to treat principle will be applied in all analysis. The primary endpoint measure is the proportion of those dead or dependent (modified Rankin scale score 0–2) at 6 months. This will be analyzed using an unadjusted logistic regression model. Binary secondary outcomes will be analyzed similarly, using analysis of variance (*t* tests) for continuous variables. For the shift analysis of modified Rankin scale using all seven categories (including 6 for death), ordinal logistic regression will be used, after verifying the proportional odds assumption. A statistical analysis plan will be completed prior to analysis and unblinding of the trial data.

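### The modified Rankin range 0–2 written beside the primary endpoint contradicts its name, death or dependency, and the protocol's own coding of death as 6

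*Protocol article*

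**What the plan says.** The endpoint is defined twice in the protocol article, with the same range each time.

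- Outcome measurement: the primary outcome is the effect of allocation on "death or dependency (a score of 0–2 on the modified Rankin scale [25]) at 6 months after randomization".
- Sample size and statistical consideration: the primary endpoint is "the proportion of those dead or dependent (modified Rankin scale score 0–2) at 6 months", to be analysed by unadjusted logistic regression.

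Two other statements fix the direction of the scale and of the hypothesis.

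- Sample size and statistical consideration, on the secondary ordinal analysis: "For the shift analysis of modified Rankin scale using all seven categories (including 6 for death").
- Abstract, Methods/design: the intervention "will reduce the composite poor outcome of death or dependency at 6 months after stroke".

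The sample size rationale follows the same direction. It takes the starting figure from earlier trials, where "the proportion of people dead or dependent at the end of follow-up was 50" per cent, and sizes the trial "to detect plausible modest 10.5 % reductions in death or dependency in the intervention group".

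**The concern.** A composite that includes death cannot be identified by scores of 0–2 on a scale where death scores 6. The range beside the endpoint describes the opposite group from the one that its name describes.

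The error is in both places where the endpoint is defined, so neither one corrects the other. It also concerns the only primary endpoint, which is binary and analysed by logistic regression. The choice of which category counts as the event sets the sign of the odds ratio. Anyone who takes the numeric range as the operative definition, when writing a data specification or comparing the trial report with the protocol, would have the direction of the main result reversed.

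This is not detail left to the SAP. The article states a cut-off, and the cut-off contradicts the rest of its text.

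**Working it through.** **Inputs, all from the protocol article**

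| Item | Value | Section |
|---|---|---|
| Range given for death or dependency | 0–2 | Outcome measurement; Sample size and statistical consideration |
| Scale | seven categories, 6 = death | Sample size and statistical consideration |
| Direction of hypothesis | poor outcome to be reduced | Abstract, Methods/design |
| Proportion dead or dependent | 50% | Sample size and statistical consideration |
| Odds reduction | 21% (odds ratio 0.79) | Background; Sample size and statistical consideration |
| Reduction used for sizing | 10.5% | Sample size and statistical consideration |
| Sample size, power, α, dropout | 600 per group, at least 90%, two-tailed 0.05, 20% | Sample size and statistical consideration |

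**Step 1: consistency of the definition.** Seven categories with 6 as the top give scores 0 to 6. Death = 6 is not in {0, 1, 2}, so the written range counts no deaths. The ordinal analysis treats the scale as an ordered measure of disability with death as the last category. The range 0–2 is therefore the end farthest from death. A set that excludes every death and holds the least disabled patients cannot be the poor outcome named in the hypothesis.

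**Step 2: the plan's own sample size.** The stated 1200 reproduces when 10.5% is read as percentage points, that is 50% against 39.5% dead or dependent.

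n per group = [z₁₋α/₂ √(2p̄(1−p̄)) + z₁₋β √(p₁(1−p₁) + p₂(1−p₂))]² / (p₁ − p₂)²

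With p₁ = 0.50, p₂ = 0.395, p̄ = 0.4475, z = 1.960 and 1.282:

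- n = 470 per group, 940 in total.
- 940 / (1 − 0.20) = 1175. With continuity correction, 489 per group gives 978 / 0.80 = 1223. Both are within 3% of 1200.
- Power with 480 per group (600 less 20%) is 0.906.

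The calculation thus treats dead or dependent as the event to be reduced. Replacing both proportions by their complements (50% against 60.5%) leaves p̄(1−p̄), both variances and the squared difference unchanged. It gives the same 470 per group and the same power. Correcting the range does not alter the sample size.

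**Step 3: effect of literal coding on the primary comparison.**

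- Odds at 50% are 1. With odds ratio 0.79, dead or dependent in the intervention group = 0.79 / 1.79 = 44.1%, a fall of 5.9 points.
- The complement = 1 − 0.441 = 55.9%. If scores 0–2 were coded as the event, the same benefit would appear as a rise from 50% to 55.9%, with odds ratio 1 / 0.79 = 1.27.
- At the difference that reproduces the sample size, a fall from 50% to 39.5% would appear as a rise from 50% to 60.5%.

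**The case against.** The strongest reply is that nobody would be misled. The endpoint carries the same name throughout, the hypothesis and the sample size rationale both speak of reducing it, and death is coded as 6. The likeliest explanation is that the favourable range was written beside the unfavourable label and then repeated. The cut-point, between 2 and 3, is the same under either label. The SAP, due before analysis and unblinding, may already code the endpoint correctly. Most of this stands: the intent can be recovered, and no error in the actual analysis can be claimed. What remains is that the prespecified numeric definition of the primary endpoint is wrong in both places. A correct SAP would then differ from the published protocol without explanation.

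Two stronger readings are tempting, and the documents do not support them.

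- A reader might take the bracket as defining dependency only, so that deaths are added to scores 0–2, and infer that benefit would again look like harm. That does not follow. Moving patients from dependent survival to 0–2 would raise such a pooled proportion, moving patients from death to dependent survival would lower it, and moving patients from death to 0–2 would leave it unchanged. The article gives no split of the 50% between death and dependency from which to settle the direction.
- A reader might infer that the published protocol cannot be used to check the reported endpoint. That goes too far, because the named endpoint and its threshold are identifiable despite the wrong range.

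**Conclusion.** The definition is wrong as written: an internal contradiction in the sole primary endpoint, present in both defining statements and corrected nowhere in the article. That conclusion needs only the article's own coding of death as 6 and its description of the composite as poor.

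If the range were applied literally, the consequence would be a reversed sign: 50% to 55.9% where the intended endpoint goes from 50% to 44.1%. Those figures assume that the 50% is the control-group rate and that the odds ratio is 0.79. They illustrate a literal coding and do not predict what the analysis will do. The sample size of 1200 is unaffected.

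That dependency means scores 3–5 is an inference from the complement and usual convention. The contradiction does not depend on it.

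**What to change.** In both Outcome measurement and Sample size and statistical consideration, state the primary event as a modified Rankin score of 3–6 at 6 months (3–5 dependent, 6 dead), with 0–2 as the favourable outcome. The sponsor should confirm the 3–5 label, since the article does not give it. Use the same coding in the SAP and the programming specification before unblinding, and say which category is the modelled event, so that an odds ratio below 1 means benefit.

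The cost is two wording changes and a published correction. Data collection, sample size and analysis method do not change. The article reports recruitment as continuing and places the SAP before unblinding, so on its own timetable the correction can be made while results are still blinded.
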